All adverse reactions manifested will be listed with detailed explanations. The frequency of abnormal reactions that are correlated with the treatment and abnormal reactions that do not have such correlations will be recorded. A Fisher’s exact test will be performed to determine whether there are any differences among the groups with respect to the incidence of abnormal reactions as reported by the subjects. Furthermore, technical analysis will be performed to identify differences in the degree of severity and in the type of abnormal reactions among the groups.

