### Adverse events

The safety evaluation will be based on adverse events, which are expected to include blisters, redness, and burns. Adverse reactions refer to undesirable and unintentional signs (e.g., abnormal test results), symptoms or diseases following the treatment. There does not necessarily have to be a cause and effect relationship with the treatment. The subjects will be instructed to voluntarily report any information regarding abnormal reactions to the practitioner on a regular basis.

Any adverse events during treatment will be recorded. When abnormal reactions appear, the date of appearance, the date of disappearance, the degree of the abnormal reaction, measures taken related to the treatment, correlation with the treatment, names of suspicious drugs taken outside of the treatment, whether the abnormal reactions were treated and any other related information will be recorded in detail. Any medical conditions or diseases present prior to the start of the treatment will be considered abnormal reactions only if they worsen after starting the treatment.

Abnormal test values or results will be considered abnormal reactions only if they cause clinical symptoms, if they are considered clinically significant or if treatment is needed.

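### The only named test of adverse-reaction incidence is worded for participant-reported reactions, which is narrower than the protocol's own definition of an adverse reaction

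*Protocol article*

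**What the plan says.** All references are to the protocol article, Methods/design.

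- **Adverse events, definition.** "Adverse reactions refer to undesirable and unintentional signs (e.g., abnormal test results), symptoms or diseases following the treatment". A causal link with treatment is not required.
- **Adverse events, test values.** An abnormal value counts "only if they cause clinical symptoms, if they are considered clinically significant or if treatment is needed". The three conditions are alternatives, so a value without symptoms can qualify.
- **Adverse events, collection.** "The subjects will be instructed to voluntarily report any information regarding abnormal reactions to the practitioner on a regular basis". The same section adds: "Any adverse events during treatment will be recorded".
- **Statistical analysis, incidence.** Fisher's exact test is to look for group differences "with respect to the incidence of abnormal reactions as reported by the subjects".
- **Statistical analysis, other handling of reactions.** "All adverse reactions manifested will be listed with detailed explanations". Frequencies of treatment-related and unrelated reactions are recorded. In addition, "technical analysis will be performed to identify differences in the degree of severity and in the type of abnormal reactions among the groups".
- **Statistical analysis, blood tests.** Blood test results are analysed with the same techniques as the main assessment variable, and the 5% level applies to all analyses.
- **Outcome measures and Table 2.** Blood tests, which include liver function and blood count, are taken at baseline and at 4 weeks.

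**The concern.** The definition and the test use different event sets. The definition is not limited by source: a sign, a symptom, a disease or a qualifying test value all count. The incidence test is worded for one source, the participant's own report. A participant cannot ordinarily be the origin of a report about a laboratory change that causes no symptoms, so such an event meets the definition and yet falls outside the test as worded.

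Two things are at stake. First, the tested incidence can be lower than the incidence under the protocol's own definition, and two analysts working from the same records could reach different numerators. Second, the control group is untreated, so participants know their allocation. A test limited to voluntary reports relies on the source most open to that knowledge. Safety is one of the purposes given in the Design section and again in the Discussion, so the incidence comparison should have one clear numerator.

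**Working it through.** The plan gives no event rate or safety sample-size figure to reproduce. The check is mainly a comparison of text, followed by an illustration on assumed counts.

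**1. Which events are in the definition, and which are in the test?**

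| Event | Adverse reaction under the Adverse events section? | Counted in the Fisher test as worded? |
|---|---|---|
| Blister, redness or burn that the participant reports | Yes | Yes |
| Abnormal test value causing symptoms that the participant reports | Yes | Yes, through the symptom |
| Symptomless test value judged clinically significant or needing treatment | Yes | No, on a literal reading |
| Skin reaction noted by the practitioner and not mentioned by the participant | Yes, as a sign | Unclear; excluded on a literal reading |

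The third row is the firm part. The qualifying rule includes "if they are considered clinically significant or if treatment is needed", which needs no symptom. The fourth row is a possible reading and not a stated exclusion.

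**2. Where else do the uncounted events appear?**

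- In the listing of all reactions, whatever the source.
- In the recorded frequencies of related and unrelated reactions, which carry no source limit.
- In the comparison of severity and type among groups, which carries no source limit but names no method.
- For laboratory changes, in the group comparison of blood test values. That compares values. It does not compare how many participants had a clinically significant abnormality, and one or two marked values among 15 may barely move a group mean.

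The gap is therefore in the incidence test alone.

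**3. How sensitive is the test to the counting rule?**

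Inputs: 15 participants per arm (Randomization section) and the three-group exact test (Statistical analysis section). The event counts are assumptions.

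With all margins fixed and T events in total, a table (a, b, c) has probability C(15,a) × C(15,b) × C(15,c) / C(45,T). The p-value is the sum over all tables with the same T that are no more probable than the observed one.

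| Counted events (A, B, control) | T | Probability of the observed table | p |
|---|---|---|---|
| 6, 6, 0 | 12 | 5005 × 5005 × 1 / 28,760,021,745 = 0.00087 | 0.011 |
| 5, 5, 0 | 10 | 3003 × 3003 × 1 / 3,190,187,286 = 0.0028 | 0.030 |
| 4, 4, 0 | 8 | 1365 × 1365 × 1 / 215,553,195 = 0.0086 | 0.097 |

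Take 6, 6 and 0 as the count under the definition. If one event per treated arm is not participant-reported, the result stays below 5%. If two per treated arm are not, it does not. If every event were a symptomless laboratory change, the literal count would be 0 in each arm. None of these rates comes from the documents.

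**The case against.** The case for leaving the wording alone has four parts.

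**Other analyses cover these events.** A reader might infer that laboratory harms drop out of the group comparison altogether, are merely listed, or could never show in a formal safety result. The documents do not support this. Blood test values are compared among groups at the 5% level, and severity and type of reactions are compared among groups with no limit to participant reports. This part of the objection stands and limits the point to the incidence test. It does not close the gap: a comparison of values is not a comparison of event incidence, and the severity and type analysis has no named method.

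**The phrase may only echo how events are collected.** Participants are told to report to the practitioner, who records the reaction, and the expected events (blisters, redness, burns) are ones that a participant sees and feels. A reader might infer that the plan excludes skin reactions seen by the practitioner. No passage says so. This stands for skin reactions, but it does not help with symptomless test values.

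**The illustration is assumed.** Both the event rate (6 of 15, or 40%) and the unreported share (2 of 6, or one third) lack a source, and with one lost event per treated arm the conclusion at 5% does not change. This stands.

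**It is a 45-person pilot, reported in a condensed article.** The primary outcome is blood pressure and is unaffected, and the all-source incidence could be rebuilt from the listing. That is fair as to weight. It does not dispose of the point, because the restricting phrase is printed in the article and disagrees with a definition printed in the same article. Nothing here depends on a missing detail.

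**Conclusion.** The point holds in a limited form. The event set of the Fisher test, the only named test of adverse-reaction incidence, does not match the protocol's definition. On a literal reading, symptomless but clinically significant laboratory abnormalities are left out of the tested incidence, and reactions noted only by the practitioner may be.

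The size cannot be fixed from the documents. The p-values show that at 15 per arm the result can depend on the counting rule; they do not predict an effect. The conclusion rests on reading the restricting phrase as written and on the premise that participants do not originate reports of symptomless test changes. The consequence is modest: it touches one safety comparison, not the primary outcome and not the recording of events.

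**What to change.** In the safety paragraph of the Statistical analysis section, state that Fisher's exact test compares the number of participants with at least one abnormal reaction as defined in the Adverse events section, from any source: participant report, practitioner observation, or a test result that meets the stated conditions. Show the participant-reported subset as a separate row.

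The cost is one sentence. Events during treatment are already to be recorded and blood tests are already scheduled, so no new data are needed. The small downside is that the reported incidence may be slightly less favourable.

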### Adverse events

The safety evaluation will be based on adverse events, which are expected to include blisters, redness, and burns. Adverse reactions refer to undesirable and unintentional signs (e.g., abnormal test results), symptoms or diseases following the treatment. There does not necessarily have to be a cause and effect relationship with the treatment. The subjects will be instructed to voluntarily report any information regarding abnormal reactions to the practitioner on a regular basis.

Any adverse events during treatment will be recorded. When abnormal reactions appear, the date of appearance, the date of disappearance, the degree of the abnormal reaction, measures taken related to the treatment, correlation with the treatment, names of suspicious drugs taken outside of the treatment, whether the abnormal reactions were treated and any other related information will be recorded in detail. Any medical conditions or diseases present prior to the start of the treatment will be considered abnormal reactions only if they worsen after starting the treatment.

Abnormal test values or results will be considered abnormal reactions only if they cause clinical symptoms, if they are considered clinically significant or if treatment is needed.

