### Interventions

#### Treatment group A

The subjects receiving moxibustion treatment will be treated 2 times per week.

During each moxibustion treatment, each acupoint will be treated five times. The moxibustion treatment will last for 25 min. The treatment will continue for 4 weeks. Following the procedures used in several previous studies [11,15,16], acupuncture needles will be inserted bilaterally into three acupuncture points (LI11, ST36, GB39) on the four peripheral extremities and unilaterally into two points (CV4, CV12) in the abdominal region. Indirect moxibustion (Manina, Haitnim Co., Ltd., Korea. 19 mm diameter and 21 mm height) will be used in the trial.

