#### Treatment group B

The format will be exactly the same as those for treatment group A, but the subjects receiving moxibustion treatment will be treated three times per week.

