### Control group (untreated group)

The control group (untreated group) will receive no treatment. The subject in this group will be asked to maintain their normal lifestyle, including diet, exercise and workload.

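### Voluntary reporting to the practitioner gives the moxibustion groups more occasions to report than controls, so the three-group test of adverse event incidence can understate non-local events in controls

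*Protocol article*

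**What the plan says.** All references are to the Protocol article.

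- **Capture (Adverse events).** "The subjects will be instructed to voluntarily report any information regarding abnormal reactions to the practitioner on a regular basis". The same section adds: "Any adverse events during treatment will be recorded". It defines adverse reactions by reference to treatment but says a causal link is not required. The expected events are blisters, redness and burns.
- **Contact (Interventions).** Group A: "The subjects receiving moxibustion treatment will be treated 2 times per week". Group B: "the subjects receiving moxibustion treatment will be treated three times per week". Duration: "The treatment will continue for 4 weeks". Controls: "The control group (untreated group) will receive no treatment".
- **Scheduled assessment (Table 2).** Adverse events are marked for all groups at week 4 and at weeks 8, 12, 16, 20 and 24. Nothing is marked between baseline and week 4. How events are asked about at these visits is not described.
- **Analysis (Statistical analysis).** A Fisher's exact test is to determine "whether there are any differences among the groups with respect to the incidence of abnormal reactions as reported by the subjects". Treatment-related and unrelated reactions are counted separately, all reactions are listed, and severity and type are compared descriptively.

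**The concern.** The quantity tested is what participants report, and the number of occasions for reporting differs by group by design. For local skin effects this matters little: controls receive no moxibustion, and a difference is real. For all-cause events that are not local, such as headache, dizziness or fatigue, a treated participant can mention a symptom within days at the next session. A control, on the schedule shown, has to remember it until week 4 or report it unprompted. Equal true incidence could then appear as an excess with moxibustion.

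Safety is a stated purpose of this pilot (Design; Discussion), and testing the methods for a later trial is another (Aims of the study). An uneven capture method would affect the safety summary here and could be carried forward. An analysis plan cannot repair this afterwards, because control events that were never reported cannot be recovered.

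**Working it through.** **1. Contacts in the treatment period.**

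- A: 2 per week × 4 weeks = 8 sessions
- B: 3 per week × 4 weeks = 12 sessions
- Control: 0 sessions, and no Table 2 visit before week 4 (inferred)

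Counting the week-4 visit, the totals are 9, 13 and 1.

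**2. Inputs for the size.** The article gives 15 per group with 20% dropout (15 × 0.80 = 12 completers) and a 5% level. It gives no event rate and no detection probability, so those below are assumptions. There is no figure in the plan to reproduce.

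**3. Direct illustration.** True incidence *t* is set equal in all groups. Observed incidence = *t* × detection, with detection 0.90 in A, 0.95 in B and 0.30 to 0.70 in controls. The rejection probability of the three-group Fisher (Freeman–Halton) test at 5% was found by exact enumeration of three binomials, 15 per group. The columns from *Control detection 30–70%* onwards give rejection probabilities.

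| True incidence | Observed A / B | Observed control | Control detection 30–70% | Control detection 90% | Full detection in all groups |
|---|---|---|---|---|---|
| 10% | 9% / 9.5% | 3–7% | 1.3–2.0% | 1.3% | 1.5% |
| 20% | 18% / 19% | 6–14% | 3.4–7.5% | 3.0% | 3.2% |
| 40% | 36% / 38% | 12–28% | 6.6–30.8% | 4.3% | 4.3% |
| 60% | 54% / 57% | 18–42% | 9.9–57.5% | 4.6% | 4.3% |

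With 12 per group the 30–70% column is about 1%, 3–6%, 5–22% and 7–42%. The test is conservative when events are rare, so the first two rows show little or no excess over 5%. The control incidence itself is understated in every row.

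**4. Illustration by number of contacts.** Let *d* be the chance that an event is reported at any one session, *s* the chance that the week-4 assessment finds it, and *m* the number of sessions. Then P(reported) = 1 − (1 − d)^m × (1 − s). Take d = 0.10, true incidence 50% and 15 per group. If week 4 is just one more voluntary contact, s = 0.10:

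- A: 0.50 × (1 − 0.9^9) = 30.6%
- B: 0.50 × (1 − 0.9^13) = 37.3%
- Control: 0.50 × 0.10 = 5%

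The test rejects in 48% of trials. If week 4 recovers 30%, 60% or 90% of events, rejection is 25%, 9% and 5%. Over true incidences of 30–70% and d of 0.05–0.20, rejection is 6–85% when week 4 is one more voluntary contact and 4–5% when it recovers 90%.

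**5. A against B.** The gap is 57% − 54% = 3 points in step 3 at 60% incidence, and 37.3% − 30.6% = 6.7 points in step 4. With 15 per group these are 0.03 × 15 ≈ 0.5 and 0.067 × 15 ≈ 1 participant.

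**The case against.** The strongest reply has four parts.

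**Control contact is inferred.** No sentence says controls are not contacted before week 4. The instruction to report regularly covers all subjects and is not tied to sessions, and the study flowchart is not available. This stands. A reader might infer that controls certainly have no means of reporting for 4 weeks; the article does not support that.

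**A common assessment exists.** Table 2 schedules adverse events for everyone at six time points, and the form of enquiry may be in the full protocol. If it is structured and sensitive, the problem nearly disappears, as the 90% results show. This limits the claim but does not answer it. The article does name a capture method, voluntary reporting, and bases the test on it. Reports from 8 or 12 sessions are still added in two groups only.

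**The expected harms are local, and the plan separates related from unrelated events.** A difference in blisters, redness or burns is genuine, and the listings let a reader see which kind of event drives a result. That helps interpretation. However, the Fisher test is not restricted to either kind, and a listing cannot show control events that were not captured.

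**It is a small pilot.** No decision rule depends on this test, and the bias tends to overstate harm from moxibustion rather than hide it. This also stands, and it keeps the point modest.

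A reader might also infer that reported events will rise from A to B because B has half as many sessions again. The calculations do not support a material effect: the gap is about 0.5 to 1 participant in the cases worked.

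**Conclusion.** The concern holds in a limited form. As written, capture by voluntary report, unequal session contact and a test on reported incidence together mix reporting opportunity with safety. The effect is on non-local, all-cause events in controls relative to the moxibustion groups. The common visits reduce it without removing it, and the A-versus-B distortion is likely small.

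The size cannot be taken from the document. Under the assumed detection rates, false rejection with 15 per group is negligible at true incidences of 10–20% (at most 7.5%). It becomes substantial only when events are common: 6.6–30.8% at 40% and 9.9–57.5% at 60%. A reader who sees only the upper figures might conclude that the test is generally invalid; that would need common events and poor detection in controls, neither of which the article establishes. The point concerns a named safety comparison, not the primary endpoint, and is worth correcting because correction is cheap.

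**What to change.** 1. At each existing Table 2 visit (week 4 and weeks 8, 12, 16, 20 and 24), ask participants in all three groups the same open question plus a short checklist, with the same recall period.
2. Base the three-group comparison of non-local, all-cause events on these common enquiries.
3. Keep every event documented at treatment sessions in the safety listing. Report local moxibustion effects (blisters, redness, burns) for A and B, by participant and per session. Restricting the whole safety analysis to common visits would be wrong, since short-lived local effects are what a 4-week recall is likely to lose.
4. State as a limitation that contact remains unequal. Treated participants may still recall better at week 4 what they already discussed at a session.

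The cost is one short form at visits already scheduled and a sentence or two in the analysis section; no extra visits are needed. The downside is that solicited questioning will raise the count of minor events in all groups. Because the article says recruitment is under way, visits completed before the change should be identified in the report.

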## Discussion

This study is a preliminary study targeting individuals with pre- or stage I hypertension, who will be randomly divided into treatment group A (2 times/week), treatment group B (3 times/week), and the control group (non-treated group). Basic analysis will be performed to assess the validity and safety of moxibustion for the treatment of pre- or stage I hypertension. The following results will be presented: the extent of stimulation provided by moxibustion, differences in the effect according to the frequency of treatment, and how long the efficacy of the treatment last. These results will be based on long-term follow-up observation.

### Trial status

This trial is currently recruiting participants.

## Abbreviations

JNC-7: Seventh Report of the Joint National Committee on the Prevention, Detection, Evaluation, and Treatment of High Blood Pressure; RCTs: Randomized controlled trials; BMI: body mass index; HRV: heart rate variability; SRI-MF: modified stress response inventory; PSQI: Pittsburgh Sleep Quality Index; FSS: Fatigue Severity Scale; EQ-5D: EuroQol; FBS: fasting blood sugar; LFT: liver function test; hs-CRP: high sensitivity C-reactive protein; HbA1C: hemoglobin A1c; CBC: complete blood count; NDI: neck disability index; ITT: intent to treat; PP: per protocol; ANOVA: analysis of variance; ABI index: ankle brachial pressure index; PWV index: brachial-ankle pulse wave velocity.
